### Follow-up

The follow-up period consists of six weeks. At fixed moments during this period (at inclusion, three days, one, three and six weeks) HRQoL questionnaires will completed. The EQ-5 D and MFI will be filled in at all these fixed moments while the SF-36 will be used one, three and six weeks postpartum.

Details of the delivery, RBC transfusion (when given) and follow-up are recorded in the CRF. During the study period all transfusion complications will be recorded. An anaemia related symptoms list is filled in before randomisation and at six weeks postpartum. Hb values will be determined at inclusion and six weeks postpartum. Six weeks postpartum patients visit the outpatient clinic.

In case of severe adverse events (SAE) during follow-up, a SAE form will be downloaded from the website and completed. SAE forms will be judged and based on this conclusion the study will be discontinued if participation in the study is considered irresponsible.

Patients that withhold informed consent for randomisation will be asked to complete the questionnaires, and case record forms (CRF) will be recorded in a similar way as patients that were randomised.

### Statistics

#### Sample size

The HRQoL assessments were tested in postpartum women in a pilot study [5]. For the comparison between RBC transfusion and an expectant management a sample size of 400 patients is planned (200 patients in the RBC transfusion group and 200 patients in the expectant management group).  Power calculations showed that with these numbers a difference of 1.3 points or greater in favour of the RBC arm regarding the physical fatigue subscale on day three, the primary outcome, can be excluded with a power of 80% at one-sided alpha of 0.025 assuming that there is no difference on this day [5]. In view of the scale of physical fatigue (ranging from 4 to 20) we think that such a difference is not clinically relevant. Since missing data are not expected to exceed 20%, a total of 500 patients will be included.

#### Data analysis

Data will be analysed according to the intention to treat principle. The primary outcome, the MFI physical fatigue score at three days postpartum, will be compared between groups using Repeated Measurement ANOVA. This analysis allows for occasional missing values and will be done using an unstructured covariance matrix, while taking account of baseline value (at t = 0) and mode of delivery as covariates. If the two-sided 95% confidence interval for the adjusted difference of means at day three excludes a difference of 1.3 points or greater in favour of the RBC arm, non-inferiority of the expectant policy is considered to be shown [17]. A per-protocol analysis, including only patients without severe protocol violations, will also be performed.

The mean profiles along time of other MFI subscales, SF-36 and EQ-5 D will be compared similarly to the primary outcome measure. The other secondary outcome measures will be assessed by calculating rates in groups, risk differences and 95% confidence interval.

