### Study design

The study is a multicentre randomised non-inferiority trial in women with an acute postpartum anaemia. It is an open label study. This trial is embedded in the Dutch Obstetric Consortium, a collaboration of hospitals in the Netherlands [11]. Approximately 40 hospitals, including university hospitals, teaching hospitals and non-teaching hospitals will participate in this trial.

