### Procedures, recruitment, randomisation and collection of baseline data

Eligible patients receive participant information. After written consent, participants are randomised by means of a web-based application [12]. Randomisation will be blocked in a 1:1 ratio for RBC transfusion or expectant management. Stratification will be applied for mode of delivery and participating hospital.

All data will be collected, coded and processed with adequate precautions to ensure patient confidentiality.

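### Hospital stratifies the randomisation but is absent from the primary model; if hospitals differ in day-3 fatigue, the decisive confidence interval is slightly conservative

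*Protocol article*

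**What the plan says.** On allocation, the section on procedures, recruitment and randomisation of the Protocol article states: "Randomisation will be blocked in a 1:1 ratio for RBC transfusion or expectant management". It continues: "Stratification will be applied for mode of delivery and participating hospital". Under Study design: "Approximately 40 hospitals, including university hospitals, teaching hospitals and non-teaching hospitals will participate in this trial".

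On the primary analysis, the Data analysis section compares day-3 MFI physical fatigue by repeated-measures ANOVA: "This analysis allows for occasional missing values and will be done using an unstructured covariance matrix". The adjustment terms are then listed: "taking account of baseline value (at t = 0) and mode of delivery as covariates". Hospital is not among them. The unstructured covariance describes repeated scores within one woman, so it does not stand in for hospital.

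The decision rests on one limit of the interval from this model. The condition is: "If the two-sided 95% confidence interval for the adjusted difference of means at day three excludes a difference of 1.3 points or greater". The difference meant is one favouring transfusion, and when the condition is met, non-inferiority is taken as shown. The other MFI subscales, the SF-36 and the EQ-5D are to be analysed in a similar way, so the same covariate list carries over to them.

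**The concern.** One of the two stratification factors is carried into the model and the other is dropped without explanation. Blocking within hospital tends to balance the arms by hospital, so differences between hospitals contribute little to the true sampling error of the treatment difference. A model that ignores hospital still counts those differences as residual variance, so its standard error is too large by whatever share of variance lies between hospitals.

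Some difference is plausible. The sites mix university, teaching and non-teaching hospitals (Study design), and iron and other anaemia medication follow local protocol (Intervention and control). The trial is planned at only 80% power and is decided by where one confidence limit falls against 1.3 points, so avoidable width is worth removing.

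**Working it through.** **Inputs from the Protocol article.** Margin 1.3 points, one-sided alpha 0.025, power 80%, true difference 0, 200 evaluable women per arm, 20% missing, 500 randomised (Sample size). About 40 hospitals (Study design). Two modes of delivery, vaginal and caesarean (Participants/eligibility criteria).

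**Not given, so assumed.** SD (solved in step 1), ICC (range 0 to 0.10), block size (4), and 20% of women in the smaller delivery-mode group.

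**Step 1: the stated sample size.** n per arm = 2 × (1.960 + 0.842)² × SD² / 1.3². With no SD stated, 200 per arm cannot be reproduced independently. Solving backwards, SD = 1.3 × √(200/2) / 2.802 = 13 / 2.802 = 4.64. The inflation reproduces exactly: 400 / (1 − 0.20) = 500.

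**Step 2: the planned interval.** SE = 4.64 × √(2/200) = 0.464; half-width = 1.96 × 0.464 = 0.909.

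**Step 3: analytic bound.** With perfect balance within hospital, accounting for hospital multiplies the SE by √(1 − ICC). Power is then Φ(1.3 / (0.464 × √(1 − ICC)) − 1.96):
- ICC 0.02: factor 0.990, half-width 0.900, power 80.8%
- ICC 0.05: factor 0.975, half-width 0.886, power 82.0%
- ICC 0.10: factor 0.949, half-width 0.863, power 84.0%

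**Step 4: simulation.** Balance is not perfect: 500 / (40 × 2) = 6.25 women per stratum, so blocks are often incomplete, and 20% of outcomes are missing. The simulation used 12,000 trials per ICC, 40 hospitals of unequal size, stratified blocks, and 500 women randomised with 20% missing at random.

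| ICC | Half-width: no hospital | random | fixed | Power: no hospital | random | fixed |
|---|---|---|---|---|---|---|
| 0 | 0.9124 | 0.9124 | 0.9311 | 79.3% | 79.3% | 78.1% |
| 0.01 | 0.9119 | 0.9087 | 0.9260 | 80.0% | 80.2% | 78.4% |
| 0.02 | 0.9122 | 0.9055 | 0.9217 | 79.8% | 80.0% | 78.4% |
| 0.05 | 0.9113 | 0.8934 | 0.9073 | 80.8% | 82.0% | 80.9% |
| 0.10 | 0.9106 | 0.8722 | 0.8834 | 80.5% | 83.3% | 82.3% |

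Excess width without hospital, relative to a random intercept:
- ICC 0.02: 0.9122 / 0.9055 = 1.007
- ICC 0.05: 0.9113 / 0.8934 = 1.020
- ICC 0.10: 0.9106 / 0.8722 = 1.044

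The Monte Carlo error of each power figure is √(0.8 × 0.2 / 12,000), about 0.4 points, so the no-hospital column agrees with the stated 80% to within about two such errors. A separate simulation of 3,000 trials per ICC gave power without and with a hospital intercept of 81.0% and 81.5% (ICC 0.02), 81.3% and 82.5% (0.05), and 80.6% and 83.2% (0.10).

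**Step 5: false non-inferiority.** With the true difference set at 1.3, the model without hospital claimed non-inferiority in 2.2% to 2.5% of the 12,000 trials at every ICC. Nominal is 2.5%, with a Monte Carlo error of about 0.14 points.

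**Limits of the check.** The 12,000-trial simulation treats day 3 on its own, without the baseline covariate, and takes the ICC as known. The relevant ICC is the one left after baseline adjustment.

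**The case against.** **No ICC is given, and evidence for a hospital effect is thin.** This stands. The variation in transfusion triggers in the Background comes from a 2003 practice questionnaire. Within the trial, transfusion is allocated and the rescue indications are common to all sites. Local iron policy remains, but nothing in the article shows that it shifts fatigue by day 3. Each woman's own baseline score may also absorb part of any hospital difference. A reader might infer that the interval is wider than the design warrants as a matter of fact; the article supports this only conditionally, and at ICC 0 nothing is lost.

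**No stated property fails.** This also stands. The Sample size section says that the margin "can be excluded with a power of 80% at one-sided alpha of 0.025 assuming that there is no difference on this day", and the model without hospital still delivers that. Power is lost only relative to a more efficient model. A reader might also infer that the error rate departs materially from 2.5%; the simulated 2.2% to 2.5% shows at most a small shift, in the cautious direction.

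**A condensed article may leave a random centre effect to an analysis plan that is not shown.** This carries some weight, but the article fixes the model down to its covariance structure and covariate list, and it names the other stratification factor. The omission is therefore in what is stated.

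**Other covariates.** A reader might go on to ask for inclusion Hb, since the Background reports a correlation with fatigue. The article does not support that step. It gives no size for the correlation and none conditional on baseline fatigue, eligibility confines Hb to 3.0 to 5.0 mmol/L, and Hb is not a stratification factor.

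**Conclusion.** The mismatch is real: the primary model leaves out one of the two factors by which women are randomised and gives no reason. Its consequence is conditional and small. For assumed residual ICCs from 0 to 0.10 and the implied SD of 4.64, the decisive interval is about 0% to 4% wider than it need be, and roughly 0 to 3 power points are forgone. Up to ICC 0.02 the power loss is below one point. Any error is conservative: it makes non-inferiority slightly harder to show and adds no risk of claiming it falsely. Low severity; a free improvement.

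**What to change.** In Data analysis, add a random intercept for participating hospital to the primary repeated-measures model, keeping baseline score and mode of delivery as fixed covariates. Use the same term for the other MFI subscales, the SF-36 and the EQ-5D. If the sponsor prefers to leave hospital out, one sentence of justification would do.

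About 40 fixed hospital effects should not be used. In the simulation they widened the interval at ICC 0 to 0.02 (0.922 to 0.931 against 0.912), whereas the random intercept never did.

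The cost is one line of wording before data lock. Hospital is already known for every woman from the randomisation, so no new data and no extra patients are needed.

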**Methods/Design:**

The WOMB trial is a multicentre randomised non-inferiority trial. Women with acute anaemia due to postpartum haemorrhage, 12-24 hours after delivery and not initially treated with RBC transfusion, are eligible for randomisation. Patients with severe physical complaints are excluded. Patients are randomised for either RBC transfusion or expectant management. Health related quality of life (HRQoL) will be assessed at inclusion, at three days and one, three and six weeks postpartum with three validated measures (Multi-dimensional Fatigue Inventory, ShortForm-36, EuroQol-5D). Primary outcome of the study is physical fatigue three days postpartum. Secondary outcome measures are general and mental fatigue scores and generic health related quality of life scores, the number of RBC transfusions, length of hospital stay, complications and health-care costs.

The primary analysis will be by intention-to-treat. The various longitudinal scores will be evaluated using Repeated Measurements ANOVA. A costs benefit analysis will also be performed. The power calculation is based on the exclusion of a difference in means of 1.3 points or greater in favour of RBC transfusion arm regarding physical fatigue subscale. With missing data not exceeding 20%, 250 patients per arm have to be randomised (one-sided alpha = 0.025, power = 80%).

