### Outcome

Primary outcome is physical fatigue on day three postpartum, scored with a dimension of the HRQoL measure MFI. We aim to show non-inferiority of the expectant management arm and therefore this primary assessment day was chosen: if there would be any difference between randomized groups, this difference is expected to be the largest three days postpartum [5]. In total three measures of HRQoL will be scored. Secondary outcomes will be the remaining HRQoL measures and the number of RBC transfusions. In addition an anaemia related symptoms list will be filled in before randomisation and at six weeks postpartum.

Medical process parameters to be evaluated include the increase of Hb level after RBC transfusion and acute transfusion complications. Moreover, we will compare the length of hospital stay and serious physical complications during the first six weeks postpartum (infections, thromboembolic events, hemodynamic events, cardiac events, neurologic events, secondary HPP, obstetric interventions, 'rescue' RBC transfusion). A costs benefit analysis will also be performed (see 'Economic Evaluation').

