#### Economic evaluation

The aim of the economic evaluation is to compare the costs and health effects of RBC transfusion versus expectant management in women with acute anaemia after PPH. As the clinical study is designed as an equivalence study, the primary economic evaluation is a cost-minimisation analysis. If RBC transfusion is shown to improve the quality of life, the economic analysis will be a cost-effectiveness analysis (time horizon: six weeks postpartum). The analysis will be performed from a hospital perspective. We will calculate direct costs (days in hospital, number of RBC transfusions and costs of complications). Real medical costs will be calculated by multiplying the volumes of health care use with the corresponding cost prices. Unit costs of health care consumption will be estimated according to national guidelines. Data on the volume of care will be available from hospital information systems in the participating hospitals.

Univariate analyses will be used for the analysis of economic outcome data. We will use non-parametric methods to test for differences between treatment groups.

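### The catch-all risk-difference rule does not fit number of transfusions or length of stay, and the cost comparison names a non-parametric test without specifying the difference in mean cost

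*Protocol article*

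**What the plan says.** **Which outcomes are secondary.** Besides the fatigue and quality-of-life scores, the abstract (Methods/Design) lists "the number of RBC transfusions, length of hospital stay, complications and health-care costs". The Outcome section is narrower: "Secondary outcomes will be the remaining HRQoL measures and the number of RBC transfusions". It then turns to medical process parameters and adds: "Moreover, we will compare the length of hospital stay and serious physical complications during the first six weeks postpartum".

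**How they are analysed.** The Data analysis section takes one group out: "The mean profiles along time of other MFI subscales, SF-36 and EQ-5 D will be compared similarly to the primary outcome measure". The next sentence covers the rest: "The other secondary outcome measures will be assessed by calculating rates in groups, risk differences and 95% confidence interval".

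**How costs are analysed.** In the Economic evaluation section, "the primary economic evaluation is a cost-minimisation analysis". Its components are given as "We will calculate direct costs (days in hospital, number of RBC transfusions and costs of complications"), each volume being multiplied by a unit price. On inference, the section mentions univariate analyses and then says: "We will use non-parametric methods to test for differences between treatment groups".

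**The concern.** There are two separate problems, and both concern what the article states rather than what it leaves out.

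First, a risk difference compares the proportions of women with an event. Complications and rescue transfusion fit that. A number of transfusions and a number of days do not, unless each is reduced to yes or no. The article names no other method for comparing these two outcomes as such.

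Second, a cost-minimisation conclusion from the hospital's perspective is about total spending, which is mean cost per woman times the number of women. The quantity needed is therefore the difference in arithmetic mean cost and its uncertainty. The article commits only to a test, of a type often carried out as a rank test. A rank test asks whether costs in one arm tend to be higher than in the other, which is a different question when costs are skewed and differently shaped in the two arms.

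The stake is the trial's secondary message. The Aims section and the abstract's Discussion both give lower cost as one of two reasons to prefer expectant management, the other being fewer transfusion reactions.

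**Working it through.** **Step 1: match each secondary outcome to its stated method.**

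| Outcome | Type | Stated method | Fit |
|---|---|---|---|
| Other MFI subscales, SF-36, EQ-5D | repeated score | as for the primary outcome | yes |
| Complications | binary | rates, risk difference | yes |
| Number of RBC transfusions | count | rates, risk difference | no |
| Length of hospital stay (secondary in the abstract) | duration | rates, risk difference | no |
| Costs | continuous, likely skewed | non-parametric test (Economic evaluation) | depends on the method chosen |

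Reducing the count to any transfusion or none would add little. Under Intervention and control, women allocated to RBC transfusion receive at least one unit and women in the other arm receive none unless rescued. The contrast would be largely fixed by allocation, apart from the rescue rate.

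**Step 2: does a rank test answer the mean-cost question?** The protocol gives no costs, so every cost figure below is an assumption. Only the 250 per arm comes from the plan: 400 evaluable / (1 − 0.20) = 500 randomised, or 250 per arm, which reproduces the stated total.

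Assume log-normal costs with log-scale SD 0.4 in one arm and 0.8 in the other. The mean is median × exp(SD²/2).

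- *Equal means of 1000.* The medians are 1000 × exp(−0.08) = 923 and 1000 × exp(−0.32) = 726. The true mean difference is 0. The rank-sum test gave p < 0.05 in 98% of 2,000 simulated trials.
- *Equal medians of 900.* The means are 900 × exp(0.08) = 975 and 900 × exp(0.32) = 1239, a true difference of 264. The rank-sum test gave p < 0.05 in 5.8% of 2,000 trials, close to its nominal level.

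So the rank test can signal a difference where mean cost has none, and can miss one where mean cost differs.

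**Step 3: does a suitable non-parametric method exist?** In the second setting, a percentile bootstrap 95% confidence interval for the difference in means covered the true value in 94.6% of 500 simulated trials.

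**Step 4: how much does the pattern of costs matter?** Take a log-normal base cost (median 1200, log-scale SD 0.5) and add 500 for every woman in the RBC arm.

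- *Expensive tail in the expectant arm only:* add 5000 in 10% of expectant women. Since 0.10 × 5000 = 500, the means are equal. The rank test rejected in 100% of trials and a Welch comparison of means in 5.7%.
- *Same complication costs in both arms:* add 5000 in 0, 5 or 10% of women in each arm, with rescue at 500 in 10% of the expectant arm. The true difference is 500 − 0.10 × 500 = 450. The rank test rejected in 100% of trials and Welch in 84 to 100%, and both pointed the same way.

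Whether the two approaches disagree, and in which direction, depends on the cost distributions.

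**The case against.** The strongest reply concerns costs. The article does not mention a rank test. A bootstrap of mean costs is itself non-parametric and fits the sentence as written, and choosing between such methods is detail that a condensed article may leave to a fuller document. Costs are in any case computed from actual volumes and prices, and a cost-minimisation analysis would ordinarily tabulate them by arm. A reader might infer that the plan can never yield a mean cost difference. The text does not support that: it leaves the quantity unspecified and does not rule it out.

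A reader might also infer that a rank test would necessarily mislead here. That does not follow either. The settings in which it does so are assumed. An expensive tail confined to the expectant arm has no support in the article: the Aims section hypothesises no important difference in physical complications, and the closing Discussion expects fewer transfusion complications and hospital days with fewer transfusions. When complication costs are the same in both arms, the rank test and the comparison of means agree.

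On the risk-difference rule, length of stay is called secondary only in the abstract. The Outcome section says merely that it will be compared, after introducing process parameters, and days in hospital also enter the economic analysis. The rise in haemoglobin might seem to be caught by the same rule, but it is listed as a process parameter and is not in the abstract's list of secondary outcomes, so it is not part of this point.

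What stands: no reading makes a risk difference suitable for number of transfusions, nor for length of stay if the abstract's list governs. The cost sentence admits one reading that answers the cost question and another that need not, and the choice should be fixed before the data are seen.

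**Conclusion.** The point holds in limited form. The catch-all rule is the wrong kind of summary for number of RBC transfusions and, on the abstract's list, for length of stay. The economic section does not specify the difference in mean cost with a confidence interval that its cost-minimisation conclusion needs. If the planned test is carried out as a rank test, it can disagree with the mean-cost comparison in either direction: 98% rejection at zero mean difference in one assumed setting, 5.8% rejection at a difference of 264 in another, and agreement in a third. These figures illustrate the mechanism and do not predict this trial's result, because the protocol gives no cost distributions. The defect is confined to secondary and economic results. The primary outcome, the non-inferiority decision and the 500 women to be randomised do not change.

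**What to change.** In Data analysis, limit rates and risk differences with 95% confidence intervals to binary outcomes, such as complications and rescue transfusion. In Economic evaluation, state that total cost, and length of stay and number of RBC transfusions as its drivers, will be compared by the difference in arithmetic means with a non-parametric bootstrap 95% confidence interval, with medians given descriptively. State also that the cost conclusion will not rest on a rank test.

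The bootstrap is compatible with the present reference to non-parametric methods, so this clarifies the economic plan more than it changes it. The cost is a few sentences of text and a little more analysis work, with no further data.
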